# Effects of Vojta Therapy on the Motor Function of Children with Neuromotor Disorders: Study Protocol for a Randomized Controlled Trial

**DOI:** 10.3390/jcm12237373

**Published:** 2023-11-28

**Keywords:** cerebral palsy, Vojta therapy, neuromotor disorder, neurorehabilitation, brain injury

## Abstract

Background: Infantile cerebral palsy is a neurological pathology that causes great morbidity, mortality, and disability in people who suffer from it, mainly affecting motor development. There are a multitude of non-pharmacological methods or therapies for its treatment. One of the main methods is Vojta therapy. This methodology acts on ontogenetic postural function and automatic postural control. Objective: This study aims to demonstrate that there are changes in the motor development of children with cerebral palsy with the application of Vojta therapy. Methods and analysis: This is a randomized controlled trial on the effectiveness of two neurorehabilitation techniques in patients with cerebral palsy conducted at the Physical Medicine and Rehabilitation Service of the Teresa Herrera Maternal and Child Hospital of the A Coruña and Cee Health Area. The study will be conducted from January 2023 to December 2024. There will be two groups: the Vojta therapy group (*n* = 30) and the conventional physiotherapy group (*n* = 30). The measurement variables will be gross motor function as measured by the Gross Motor Function Measure (GMFM) and Infant Motor Profile (IMP) scales. Ethics and dissemination: The study was approved by the Research Ethics Committee of the University of Murcia (1823/2018) and Comité de Ética de la Investigación de A Coruña-Ferrol (2022/099). Trial registration number: ClinicalTrials.gov; identifier: NCT06092619.

## 1. Introduction

Considering the time and effort that families of children with cerebral palsy invest in physical therapy, it is important to know whether more frequent interventions really improve gross motor performance. Some recent studies suggested that high-frequency physical therapy should be considered when gross motor improvement is prioritized [1,2,3]. Motor learning theories highlight the need for high-frequency repetitions for motor learning to occur. Due to these recommendations, most children with cerebral palsy are immersed in goal-directed, task-specific practice with frequent repetitions. Nevertheless, multiple environmental factors [4] may affect gross motor progress, including how everyday skills may be integrated into daily routines, thereby providing additional therapy and making it difficult to understand how much progress come directly for physical therapy intervention [5]. On the other hand, Vojta therapy (VT) was developed by [name] and uses locomotor patterns activated “reflexogenically”. This methodology acts on the ontogenetic postural function and automatic postural control [6], on which different environmental aspects will later act. Also known as “Reflex Locomotion”, it does not refer to neuronal regulation but is rather related to therapeutically applied external stimuli and their automatic movement responses. VT was developed by the Czech professor and pediatric and adult neurologist Vaclav Vojta in the 1960s. Most of his rehabilitation work and the development of the Vojta principle was developed in Germany, where he emigrated due to the political situation in Europe after the Second World War. The physiotherapy developed by [name] using “reflex locomotion” is based on his findings on the development of posture and movement in children. He discovered the basis of this therapeutic intervention while searching for treatment possibilities for young people with CP and spastic paralysis [7]. His approach was founded in years of systematic neurokinesiological observation and examination of children with typical and atypical development. He observed that sustained stimulation of peripheral pressure elicited a stereotyped full-body motor response, manifested as a pattern of tonic and phasic muscle contractions on both sides of the neck, trunk, and limbs, resulting from spatial and temporal summation that leads to improved postural control [6]. Therapists administer pressure to defined zones on the body in a patient who is in a prone, supine, or side-lying position. Two main movement complexes are used therapeutically: “reflex creeping” in a prone lying position and “reflex rolling” from a supine and side-lying position [7,8], The afferent input of VT therapy generates important cortical and subcortical changes, especially in the ipsilateral putamen [9]. The resulting outputs are differential responses that seem to be located in the brainstem and cerebellum, pontomedullary reticular formation, and posterior cerebellar hemisphere and vermis [10], causing muscle contractions in various muscle groups [11]. Studies using EEGs show changes in motor areas, indicating the activation of innate locomotor circuits [12]. These automatic motor patterns aim to change task-related motor activation and its associated postural control, as well as to release and facilitate the development of the ontogenetic postural function [13,14]. Therapeutic components, such as inhibition of abnormal movement patterns, and facilitation of normal movement patterns and physical guidance, have been attributed to VT [15], and are included within the body structure, function, and activity components of the International Classification of Functioning, Disability, and Health (ICF) [16]. Parental education is also a baseline contextual factor within this framework in VT [15].

Children with CP have specific deficits of postural control in standing or walking, including reduced stability of the axial segments. This results in a set of persistent atypical movements and posture, which prevent balance, as well as fluid and selective movements. Compensatory postural strategies described as “on bloc movements” are often observed, such as non-selective swinging between the head and trunk as a single segment to achieve forward propulsion without losing balance [17]. These compensatory strategies must be identified and considered in rehabilitation programs for CP children. These aspects may be improved with rehabilitative interventions focusing on postural control and trunk activity [18,19]. 

For this reason, studies involving intervention with Vojta therapy, which follows these same principles, also seem to demonstrate its effectiveness in these aspects. VT is a commonly extended tool in the field of pediatric rehabilitation [6,20]. Numerous studies have reported improvements in the acquisition of sitting in infantile cerebral palsy [21], gait acquisition [20,22], improving gait kinetics and kinematics [23,24,25], as well as stability, trunk balance, and spinal symmetry [26,27]. Furthermore, Vojta therapy is considered to be one of the most recommended techniques for the treatment of respiratory disorders in infantile cerebral palsy [28]; it has proven to be the technique of choice in respiratory physiotherapy as it has been shown to improve compliance, SO2, and SpO2 by reducing the respiratory frequency without increasing PCO2 [29,30,31]. Furthermore, previous research showed how VT accelerates the acquisition of GMFM-88 items and locomotor stages in children with cerebral palsy younger than 18 months by activating the postural control required to achieve the uncompleted items. This work pointed to the need to develop future studies analyzing the effects of VT at different treatment dosing, with blind assessments and larger samples [6]. Previous studies described significant differences in GMFM sitting after VT, even if the total score of the GMFM-88 did not [21]. VT has been reported to be clinically beneficial for strength, movement, and motor activities in individual cases [32] and is being considered within the second of three levels of evidence in interventions for cerebral palsy [33]. Poor study design has cast a shadow over the positive results in previous studies about VT, including a lack of random sequence generation, concealed allocation, study blinding, incomplete outcome data collection, and selective reporting [33]. On the other hand, a randomized controlled trial showed improvements in postural control and motor function early rehabilitation of adults with acute stroke [34,35]. The ethical limitations of randomized untreated control groups or placebo interventions limit the quality of the intervention in this field. Baseless attributed child distress [33] has been found in the literature [36,37,38], and bonding facilitation due to an integrative approach of the family in the rehabilitation process has also been described [37]. Family participation in the decision-making process is highly emphasized [39], and its integration on the therapeutic handling reduces economic cost and commuting times and increases the dosing possibilities. 

Because functional training of compensatory strategies is not emphasized, gross motor improvements after VT intervention seems to depend on the activation of the postural frame required for their acquisition, reducing compensatory strategies during the subsequent environment exposure. Our hypothesis is that there is an improvement in the postural function and, therefore, on the rate of acquisition of gross motor function from the first weeks of application of reflex locomotion therapy in children with neuromotor disorders. The purposes of this trial were to understand the effect of reflex locomotion therapy on the GMFM of children with cerebral palsy without specific training of its items, as well as to understand what role is played by its dosage. 

### 1.1. Hypothesis

“Vojta or Reflex Locomotion therapy improves the rate of development of gross motor function in babies and children with neuromotor disorders”.

### 1.2. Main Goal

This study aims to demonstrate that there are changes in the motor development of children with cerebral palsy with the application of Vojta therapy by quantifying the impact on the rate of development of gross motor function in children younger than 36 months of age with neuromotor disorders.

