### 1.3. Secondary Goals

To understand the effect of both the dosage of hospital treatment and home treatment by parents (economic analysis/resource efficiency).To study the natural history of the rate of development of gross motor function in children under one and a half years of age with neuromotor alterations (pre-rehabilitation intervention).To assess the long-term impact on the gross motor function of children with neuromotor disorders undergoing Vojta therapy compared to children treated without this methodology.

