#### 2.3.2. Exclusion Criteria

The data of those patients who have had to apply another therapy (pharmacological, surgical, or rehabilitative) during the care provided by the physiotherapist in their usual clinical practice will not be included. For ethical reasons, this will not be explicitly explained to the families who agree to participate in this study, so as not to influence possible therapeutic decisions in the following two months. Data of the children will be followed up and can be excluded later if there is a change in their diagnosis and cerebral palsy is not confirmed at the appropriate age. The previous therapeutic trajectory, as well as concomitant treatment (such as pharmacological treatment for spasticity, dystonia, epilepsy, etc., as well as other rehabilitation interventions) was not considered within the exclusion criteria for two reasons: their effect would already be included within the rate of motor development before VT, and also because all the children were compared only to themselves. These will be noted and considered during the calculations, but the data exclusion will only occur if there are changes in them (both adding or withdrawal) during our 2 months of intervention. 

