### 2.6. Sample Size Calculation and Statistical Analysis

Sample size calculation: The prevalence of cerebral palsy is 2.08 cases/1000 births. To obtain a good sample security, 30 subjects for each of the groups to be evaluated offer a confidence interval of 95% with a security of 10.

The initial GMFM and IMP score will be divided by the child’s months of age to calculate the rate of acquisition of their items so far. This calculation represents the mean distribution of the acquisition of these motor items. The acceleration values will be used to avoid errors in the assumption of how these items were acquired, since the tendency is to be exponential at these ages. The net values obtained in the valuation will not be considered, but the rate with which they have been obtained as a function of time will be. The rate of this development without intervention will be calculated at the time of the initial assessment, relative to the age of the patient. The proportion of the score necessary to obtain in the next two months to be able to accelerate that rate, instead of following the same previous trajectory, will be an unknown concept for all therapists and examiners.

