## 3. Methods and Timeline

Phase 1. Initial Assessment: Children who go to the rehabilitation center where they have been referred will be treated, an initial routine clinical examination will be performed, including: Personal/medical data collection.GMFM quantification.Treatment with the physiotherapist.Training of the parents in the home program.Recording for the IMP quantification.

Phase 2. Intervention period (2 months): The assignment to the therapist will be randomized according to the needs of the service, where each therapist will adapt the treatment according to the initial assessment. Both assessors and therapist cannot be blinded to the allocation or treatment, and both required live-direct performance. An external assessor (blind to both) will be able to score the IMP recordings. 

Children will receive weekly or fortnightly treatment, and their parents, family members, or carer will be trained in carrying out a home program. Each therapist will adapt the treatment according to the initial evaluation, as is usually performed in the rehabilitation service. During the treatment sessions, the physiotherapist will apply the therapy directly, either based on Vojta therapy or conventional physiotherapy. The frequency of repetition of the treatment at home and in the hospital will be recorded, depending on the availability of each family and the normal functioning of the service.

Phase 3. Second assessment at 2 months (±1 week, depending on follow up appointments).

Collection of data on the possible changes made in previous treatments and the frequency of home treatment (possible incidents due to illness or family limitations).GMFM quantification.Recording necessary for IMP quantification.

Children carried on clinically with the intervention, but this short period would allow us to attribute changes to RL, controlling better the influence of other factor (such as age maturation or other therapy inputs).

Study length. The data collection will be carried out for 4 years from the approval of the CEI. Only patients receiving healthcare with any of the therapies under investigation after authorization by the CEI will be included.

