### Statistical Methods

Statistical analysis will be performed using the SPSS 27.0 statistical software for Windows (SPSS Inc., Chicago, IL, USA; version 27.0). The normality of the sample will be checked using the Shapiro–Wilk test, and if it follows a normal distribution, an analysis of variance (ANOVA) of repeated measures p will be used, with time (pre-treatment and post-treatment) as an intra-group factor, and Vojta and conventional physiotherapy groups as the inter-group factor, all with a Bonferroni correction. Statistical analysis will be performed with a confidence level of 95%, so a *p*-value of <0.05 will be considered significant.

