The rate values are calculated by dividing the total score by the time (days of age) required to achieve it, assuming that the neonatal GMFM would be zero. The acceleration factor is calculated by dividing the differences between final and initial rate (assumed to be zero at birth), by the age in days (elapsed time). The same rate and acceleration factors of acquisition are figured out between the initial assessment and after two months of the intervention. Only new points acquired during this period were considered to calculate the rate of development and acceleration values in the intervention period. Because the distribution of the item acquisition during the pre-intervention period is unknown, we performed a second rate calculation assuming that all the items were adquired during the last two months before the intervention (for children older than 2 months at initial assessment). This simulation of the maximal possible pre-intervention rate and acceleration will limit the possibility of being overcome by the post-treatment values and will avoid average values slowing down the last two preintervention months. Completing all the items in the previous two months is unlikely and would make it more difficult to obtain improvements after the intervention, especially for the older children. Even if these calculations do not benefit our results, they will ensure that the rate and acceleration post-intervention can be compared within same-lasting and following periods. We know that the GMFM item acquisition is not linear, and both calculations will help us to understand if the rate differences are due to natural acceleration or a significant therapeutic change. On the other hand, this will avoid comparing low average rate values due to longer pre-intervention periods and, therefore, random positive outcomes. Rate values within each GMFM dimension will then be considered and will help to clarify the results. 

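### The main question has two conflicting references, the child's own earlier rate and the control arm, and the time-by-group effect is never made the deciding test

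*Protocol article*

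**What the plan says.** **Statements that point to a within-child comparison**
- Section 1.1: the hypothesis is that Vojta therapy "improves the rate of development of gross motor function in babies and children with neuromotor disorders". It does not say relative to what.
- Section 1.2: the main goal is to "demonstrate that there are changes in the motor development of children with cerebral palsy with the application of Vojta therapy", by quantifying the effect on the rate of gross motor development under 36 months of age. No comparator is named.
- Section 2.3.2: earlier and concomitant treatment is not an exclusion criterion, partly because "all the children were compared only to themselves".
- Section 3, on the 2-month follow-up: "this short period would allow us to attribute changes to RL".
- Section 4: the rate and acceleration in the intervention period are set against two versions of the child's own pre-intervention values. It says that "both calculations will help us to understand if the rate differences are due to natural acceleration or a significant therapeutic change". The control arm plays no part in that argument.

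**Statements that point to a between-arm comparison**
- The Abstract and section 2.1 describe a controlled trial with a Vojta group and a conventional-physiotherapy group, 30 children each.
- Statistical Methods specifies a repeated-measures ANOVA "with time (pre-treatment and post-treatment) as an intra-group factor, and Vojta and conventional physiotherapy groups as the inter-group factor". It does not mention the time-by-group effect or say which effect answers the hypothesis.
- Section 1.3 has the only objective that compares children "undergoing Vojta therapy compared to children treated without this methodology". It is secondary and concerns long-term impact.

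On natural growth, section 2.6 uses acceleration values "since the tendency is to be exponential at these ages".

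**The concern.** The two sets of statements lead to different conclusions from the same data. A two-by-two repeated-measures ANOVA gives three effects. The time effect measures change averaged over both arms. The group effect compares overall levels and carries any baseline difference between the arms. Only the time-by-group effect asks whether the change differs between Vojta and conventional physiotherapy.

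If the within-child statements govern, the control arm has no role in the main conclusion. The article itself expects acquisition to speed up at these ages, so a child's rate may exceed its earlier average under any therapy, or under none. Section 4 discusses what would follow if the hypothesis is confirmed but gives no criterion for confirmation. At stake is whether common acceleration in both arms could be reported as an effect of Vojta therapy.

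**Working it through.** **Inputs from the article.** 30 children per arm (2.6); a 2-month interval (3); significance at p < 0.05 (Statistical Methods), taken as two-sided because the side is not stated; ages up to 36 months (2.3.1).

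**The plan's own figure.** The only relevant figure is 30 per arm, and it supplies no effect size, SD or power. The stated basis (prevalence 2.08 per 1000, 95% confidence, a security of 10) does not lead to 30 by the usual precision formula. If the security figure is read as ±0.10, n = 1.96² × 0.00208 × 0.99792 / 0.10² = 0.8; with p = 0.5, n = 96. Effect sizes below are therefore assumptions. The point does not depend on how 30 was reached.

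**Step 1: can the rate rise without a treatment effect?** Suppose the untreated score is proportional to age^k, with age a in months (assumed shapes).
- Average pre-intervention rate: a^k / a.
- Rate over the next 2 months, new points only: ((a+2)^k − a^k) / 2.
- Upper-bound pre-intervention rate from section 4 (all points gained in the last 2 months): a^k / 2.

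Example, k = 2 and a = 12: intervention-period rate (196 − 144)/2 = 26; average pre-rate 144/12 = 12; ratio 26/12 = 2.17. The upper-bound pre-rate is 144/2 = 72; ratio 26/72 = 0.36.

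| Growth shape | Ratio to average pre-rate, ages 6 / 12 / 24 | Ratio to upper-bound pre-rate, ages 6 / 12 / 24 |
|---|---|---|
| k = 0.7 (decelerating) | 0.67 / 0.68 / 0.69 | 0.22 / 0.11 / 0.06 |
| k = 1 (linear) | 1.00 / 1.00 / 1.00 | 0.33 / 0.17 / 0.08 |
| k = 1.5 | 1.62 / 1.56 / 1.53 | 0.54 / 0.26 / 0.13 |
| k = 2 | 2.33 / 2.17 / 2.08 | 0.78 / 0.36 / 0.17 |

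Under accelerating growth, the direction the article expects, the rate rises to about 1.5 to 2.3 times its earlier average with no treatment effect. Against the upper-bound pre-rate it never rises in these cases.

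**Step 2: which tests respond when both arms change equally?** Let d be the mean pre-to-post change in the analysed rate, in SDs of change, identical in both arms (assumed range).
- Within-Vojta paired test: noncentrality d√30, 29 df. At d = 0.5 this is 2.74.
- ANOVA time effect: noncentrality d√60, 58 df. At d = 0.5 this is 3.87.
- Time-by-group effect: noncentrality 0, because the arms do not differ.

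| d | Within-Vojta significant | Time effect significant | Time-by-group significant |
|---|---|---|---|
| 0.3 | 36% | 63% | 4.9% |
| 0.5 | 75% | 97% | 4.7% |
| 0.8 | 99% | 100% | 5.1% |

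These are results from 20,000 simulated trials per row.

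**Step 3: what can the arm contrast detect?** By normal approximation, the detectable difference at 80% power is (1.96 + 0.84) × √(2/30) = 2.80 × 0.258 = 0.72 SD of change. Power is 49% at 0.5 SD and 21% at 0.3 SD. A difference of 0.5 SD would need 63 per arm for 80% power.

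**The case against.** **The outcome is a rate, not a gain.** A reader might infer that the trial would declare success whenever children develop. The article does not support that. Section 2.6 says net scores will not be considered, and section 4 uses only newly acquired points. Steady growth gives a ratio of 1.0 and decelerating growth about 0.7, so ordinary development alone does not show improvement. The upper-bound pre-rate is stricter still. This objection stands against the stronger reading. It does not remove the problem: under accelerating growth the average-rate comparison still rises unaided. The upper-bound calculation is only a partial guard. It is one of two calculations, it is not made decisive, and it is not a comparison with the control arm.

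**The control arm is in the plan.** This is true. The ANOVA includes group, so the interaction is available, and an analysis plan that is not shown may name it. If silence about the deciding effect were the only fault, there would be no finding. The fault is that the stated goal, the self-comparison and the attribution to reflex locomotion point elsewhere. Naming the interaction in another document would leave that conflict in place.

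**The quoted sentences have other purposes.** The self-comparison sentence justifies an eligibility choice, and the attribution sentence justifies a short follow-up. Neither is a success rule, and the article states none. So it can be said only that a within-arm rise could be read as confirmation, not that it would be.

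**Conclusion.** The concern holds in this limited form. The article gives two incompatible references for its main question, and the only effect that uses the control arm to separate therapy from common growth is not made decisive. The conflict is between statements in the text and is not a matter of missing detail.

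The size depends on assumptions. The 1.5- to 2.3-fold rise requires accelerating growth of the assumed shapes and the average pre-rate as reference. The significance percentages require a positive mean change in the analysed rate of 0.3 to 0.8 SD in both arms. If growth were linear, or the upper-bound pre-rate were the reference, a spurious rise would not be expected. The time-by-group effect stays at about 5% for any change that both arms share. It does not by itself remove bias from the way the arms are formed, which is a separate matter.

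**What to change.** 1. In sections 1.1 and 1.2, state that the change in rate (and acceleration) of gross motor acquisition over the 2 months is larger under Vojta therapy than under conventional physiotherapy. Keep the rate outcome; wording in terms of raw gain would conflict with sections 2.6 and 4.
2. In Statistical Methods, name the time-by-group effect on that rate outcome, with its 95% confidence interval, as the test of the hypothesis. Treat the time effect, the group main effect and within-arm comparisons as descriptive.
3. In section 2.3.2, reword the self-comparison statement. In section 3, reword the attribution to reflex locomotion so that it rests on the between-arm difference.

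**Cost.** This needs only wording and no new data. It is best done now, since section 4 reports completed assessments for only four children; choosing the deciding test after results are known would be post hoc. A within-arm change alone could no longer be reported as confirming the hypothesis. The investigators would also have to accept the power of the arm contrast shown above, or revisit the sample size.
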